### Step 2-
Cabotegravir safety, growth pattern and development study

We hypothesise that there will be no difference in the incidence of adverse events or illnesses, growth, and development between infants exposed to breast milk CAB and those exposed to breast milk oral PrEP. 25 mother-infant pairs from Step 1 (mothers receiving CAB for PrEP), 25 other mother-infant pairs from the oral PrEP group of the PathToScale and LINK studies and 50 mother-infant pairs naïve of PrEP, matched to those in the CAB PrEP group, will be followed up for eight months from the time of maternal PrEP initiation in the PrEP groups or a similar time in the PrEP naïve group. The PathToScale and LINK studies are following up mothers in the CAB group from the initiation visit, 1 month later and, thereafter, every 2 months. In our study we will follow a similar schedule for all three groups with a final exit visit scheduled at eight months post initial CAB dose. This will result in 10 scheduled visits in the CAB group and six in the oral PrEP and no PrEP groups. The CAB LA PrEP group will have four additional visits for PK sampling at month 7. In the present CABMILK Study, we will utilise all six planned visits to assess the incidence of reported adverse events and infant growth by measuring anthropometric indices (weight-for-height and height-for-age) as well as head circumference-for-age. The same visit schedule and safety assessments will be applied to the oral PrEP and PrEP-naïve groups. Infant growth and neurodevelopment will be longitudinally assessed at all six study visits using the Caregiver Reported Early Development Instrument (CREDI).

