### Sample size determination and power calculation

Sample size calculation has been primarily based on step 1 of the CABMILK study. Step 2 leverages on the previous step. In Step 1 (Cabotegravir maternal, breastmilk and infant pharmacokinetic study), previous data on 600 mg intramuscular CAB in adults yielded an area under the concentration-time curve (AUC0-∞, μg*h/mL, [range]) of 4172 [2839–6597] with a coefficient of variation of 24%.
^17^ Assuming a similar coefficient of variation, the inclusion of 25 breastfeeding infants will provide >95% precision to estimate overall infant CAB exposure.

Step 2 (Prospective observational cohort follow-up of mother–infant pairs): Detecting rare safety outcomes or subtle neurodevelopmental effects related to cabotegravir exposure would require substantially larger and longer-term studies. Accordingly, Step 2 is designed as a prospective observational cohort to describe infant exposure and characterise safety signals rather than to support formal inferential comparisons. Safety outcomes will include reported adverse events, growth patterns, and changes in developmental status over time.

We plan to enrol 100 mother–infant pairs (25 CAB-LA, 25 oral TDF/FTC PrEP, and 50 PrEP-naïve). This sample size is intended to provide a reasonable descriptive profile of safety and developmental outcomes across exposure groups. The larger PrEP-naïve group will support more stable estimation of background patterns against which findings in the exposed groups can be contextualised.

Child development will be assessed using the CREDI Short Form, a caregiver-reported tool that provides a summary developmental status score suitable for population-level description rather than clinical diagnosis. Assessments over 8 months of follow-up will allow characterisation of short-term developmental trajectories, while recognising that longer-term outcomes cannot be determined within this study.

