Comparative analyses will be exploratory. Longitudinal growth indices will be analysed using linear mixed-effects models (or generalized estimating equations) to account for repeated measures, and developmental status (continuous CREDI summary score) will be compared across groups using adjusted regression models. Because exposure groups are not randomised, analyses will be interpreted as observational associations and adjusted for prespecified maternal and infant confounders. Results will emphasise effect sizes and confidence intervals. We acknowledge that the study is not powered to detect subtle differences, rare events, or long-term neurodevelopmental outcomes, and findings will therefore be interpreted cautiously and used to inform the design of future larger studies.

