## Limitations

This study has several limitations. Enrolment from birth to five months spans a period of rapid ontogeny of Uridine Diphosphate Glucuronosyltransferase 1A1 (UGT1A1)-mediated glucuronidation and developmental change. Although population pharmacokinetic modelling incorporating maturation functions and age-standardised growth and developmental outcomes will be used, the small number of infants within age strata limits precision in characterising exposure–age relationships; findings at younger ages should therefore be interpreted with caution. Secondly, the study is not powered to detect between-group differences in infant safety, growth, or developmental outcomes, and these analyses are consequently descriptive and hypothesis-generating, with formal inference deferred to larger studies. Thirdly, infant feeding patterns and maternal nutritional status may influence infant exposure; feeding will be captured longitudinally and incorporated as a time-varying covariate, while maternal weight will be evaluated in relation to cabotegravir clearance and milk-to-plasma ratios. However, the study does not directly measure milk composition or detailed maternal dietary intake, limiting the ability to fully assess indirect dietary effects. Finally, as exposure groups are self-selected, comparative analyses are observational and exploratory, and although adjusted and sensitivity analyses will be undertaken where feasible, residual confounding cannot be excluded.

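### Step 2 states a no-difference hypothesis, and Table 2 tests it, although the rest of the protocol makes Step 2 descriptive and unpowered for between-group comparison

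*Protocol article*

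**What the plan says.** The protocol article speaks in two ways about Step 2.

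**As a hypothesis with tests.** The Step 2 section sets CAB against oral PrEP, both received through milk: "We hypothesise that there will be no difference in the incidence of adverse events or illnesses, growth, and development between infants exposed to breast milk". Table 2, in the row on infant safety outcomes, then plans independent t-tests on mean anthropometric indices and Chi-squared tests on overall morbidity, both across the three groups. The outcome named for that row is the effect of milk CAB on growth and neurocognitive development relative to daily oral PrEP, which is the contrast in the hypothesis.

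**As description.** The sample size section takes its number from the pharmacokinetic step: "Sample size calculation has been primarily based on step 1 of the CABMILK study. Step 2 leverages on the previous step". It says Step 2 is there "to describe infant exposure and characterise safety signals rather than to support formal inferential comparisons", and concedes that "the study is not powered to detect subtle differences, rare events, or long-term neurodevelopmental outcomes". The second specific aim promises effect sizes with 95% confidence intervals and no formal between-group testing. The Data analysis section makes the primary safety results descriptive, excludes p-values for group comparisons, and leaves formal safety inference to larger studies. The Limitations section repeats that "the study is not powered to detect between-group differences in infant safety, growth, or developmental outcomes".

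No tolerable difference, error rate, power, effect size or event rate is given for any Step 2 outcome.

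**The concern.** A hypothesis of no difference is the null hypothesis of the tests in Table 2. If those tests are run as written, the result that agrees with the hypothesis is a failure to reject. In groups of 25 that failure is likely whether or not a relevant harm exists, so it carries little information.

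The two descriptions of Step 2 also lead to different reports. An analyst who follows Table 2 produces p-values set against a hypothesis stated in advance. An analyst who follows the second aim and the Data analysis text produces differences with intervals and no tests. The Conclusion section expects the results to inform the national rollout and future WHO recommendations, so it matters which report is written.

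**Working it through.** **1. The passages side by side**

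| Topic | Step 2 section and Table 2 | Objectives, Sample size, Data analysis, Limitations |
|---|---|---|
| Purpose | No difference, CAB versus oral PrEP | Describe patterns and signals |
| Growth | Independent t-tests | Mixed-effects models; effect sizes and 95% CIs |
| Adverse events | Chi-squared tests | Counts, exact 95% CIs, rates and Kaplan–Meier curves; no group p-values |
| Inference | Implied by hypothesis and tests | Deferred to larger studies |

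The growth and adverse event rows cannot both be followed. For CREDI, Table 2 already asks for adjusted mean differences with 95% CIs, so it agrees with the rest of the protocol there.

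**2. What the tests could show**

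The protocol gives no Step 2 figure to reproduce. From the documents: "We plan to enrol 100 mother–infant pairs (25 CAB-LA, 25 oral TDF/FTC PrEP, and 50 PrEP-naïve"), so the hypothesised contrast is 25 versus 25. My assumptions, for illustration only: two-sided 5% level, outcome SD of 1, one visit, no adjustment, and the effects and event proportions shown below.

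*t-test.* Noncentrality = d × √(n/2) = 0.5 × √12.5 = 1.77; critical value t(48) = 2.01.
- Power at 0.5 SD = 0.41, so such a difference is missed 59% of the time.
- Power at 0.8 SD = 0.79; 80% power needs 0.81 SD.

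*Chi-squared test, uncorrected, by exact enumeration of all 26 × 26 outcomes.*
- 20% versus 40%: power 0.352, non-significant 65% of the time.
- 10% versus 20%: power 0.174, non-significant 83% of the time.

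**3. What the intervals could show**

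- Mean difference, one visit: half-width = t(48) × √(2/25) = 2.011 × 0.283 = 0.57 SD.
- Mean difference averaged over six visits: 0.569 × √[(1 + 5ρ)/6], where ρ is the within-infant correlation. The protocol gives no ρ. At ρ = 0.4 this is 0.569 × √0.500 = 0.40 SD; at ρ = 0.8 it is 0.569 × √0.833 = 0.52 SD.
- Risk difference with the same proportion p in both groups: 1.96 × √[2p(1 − p)/25], or 17 percentage points at p = 10% and 28 points at p = 50%.
- No events among 25 CAB infants: exact two-sided 95% upper limit = 1 − 0.025^(1/25) = 13.7%. This needs only n = 25.

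**The case against.** The strongest reply is that Step 2 does not rest on the hypothesis sentence. Its size comes from Step 1, the absence of power is admitted more than once, and the comparative work is called exploratory and is to be interpreted cautiously. Effect sizes with intervals are already promised. On this view one leftover sentence is overridden by the rest of the text.

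Much of this stands, and it rules out three stronger readings that a reader might infer.

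- *That Step 2 is built on the hypothesis.* No Step 2 number depends on it.
- *That a missing margin is a fault.* Margins belong to non-inferiority or equivalence designs. A descriptive cohort that defers inference needs none.
- *That the investigators plan to conclude safety from non-significance.* No section says so.

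A further fair point is that the 0.57 SD and the power figures describe one unadjusted visit, whereas the plan for growth and CREDI is a longitudinal model. A visit-averaged contrast would be more precise, as the working shows.

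The reply does not remove the contradiction. The disclaimers are what the hypothesis sentence and the Table 2 tests conflict with, and both remain in the current text. Admitting low power also does not tell a reader how large a harm the data leave open.

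**Conclusion.** The point holds as an internal contradiction that affects what is analysed and concluded. The Step 2 section states a null hypothesis and Table 2 tests across the groups, while the objectives, sample size, data analysis and limitations sections say there will be no formal between-group testing and no power for it.

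A non-significant result from 25 versus 25 infants could not support the hypothesis. Power is about 41% for 0.5 SD and about 35% for 20% versus 40%, under the assumed effects and a single-visit, unadjusted comparison. These figures are illustrations and do not describe the precision of the planned mixed models. Only the 13.7% limit for zero events in 25 is free of such assumptions.

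The documents do not support saying that Step 2 is wrongly sized, that it lacks a required margin, or that it plans to infer safety from a failure to reject.

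**What to change.** 1. **Step 2 section.** Replace the hypothesis with an estimation aim: the CAB minus oral PrEP and CAB minus PrEP-naïve differences in adverse events, growth and CREDI scores, each with a 95% confidence interval.
2. **Table 2.** Replace the t-tests and Chi-squared tests with the estimates and intervals already planned in the second specific aim, the sample size section and the Data analysis section.
3. **Interpretation.** State in advance that an interval including zero will not be read as no difference or as safe. For each outcome report the unfavourable confidence limit, that is, the largest harm that the interval does not exclude.
4. **Sample size section, optional.** Print the 13.7% upper limit for zero events in 25 beside the Step 2 numbers. If a half-width in SD units is given, label it as an assumption-based single-visit figure (about 0.57 SD) that would be smaller under the planned repeated-measures model.

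The cost is wording, with no margin, extra infants or new data. The Study status section says enrolment is ongoing, so the change can be made before analysis. What is given up is the option of reporting a result as agreeing with a hypothesis of no difference.

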### Inclusion and exclusion
*criteria*

*The inclusion criteria of the study are:*

Eligible participants will be breastfeeding mother–infant dyads recruited from health facilities participating in the PathToScale and LINK implementation studies. Inclusion criteria are designed to identify HIV-negative breastfeeding mothers with anticipated or documented exposure to oral or long-acting injectable cabotegravir for HIV pre-exposure prophylaxis (PrEP), while ensuring the feasibility of pharmacokinetic sampling and infant safety follow-up.

Specifically, eligible mothers will be HIV negative, aged 15 years or older and are either: (i) intending receive oral or injectable cabotegravir PrEP under government facilities which maybe PathToScale or LINK studies implementation sites, or (ii) HIV-negative breastfeeding mothers attending postnatal or under-five clinics at participating facilities. Mothers will be expected to be willing and able to comply with all study procedures as described in the Participant Information Leaflet (PIL) and to provide written informed consent for themselves and their infants or assent for participants less than 18 years of age. It will be expected that infants remain within the infant age range at the time of planned mother–infant pharmacokinetic sampling to allow adequate assessment of cabotegravir exposure and safety outcomes. As such enrolment for eligible mother-infant pairs shall occurs from the first week of birth to less than 5 months.

*The exclusion criteria of the study are:*

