### Data analysis

Data will be analysed using either STATA or R.
Table 2 outlines the planned data analyses stratified by the specific objectives of the study. Infant age at every sampling occasion and at every safety and developmental assessment will be recorded to the day. Both postnatal age (PNA) and postmenstrual age (PMA = gestational age at birth + PNA) will be derived for each timepoint and treated as time-varying variables. The population pharmacokinetic model (NONMEM/Monolix) will incorporate, as fixed structural features, allometric size scaling (exponent 0.75 on apparent clearance, 1 on volume of distribution) and a sigmoidal maturation function on apparent clearance, with PMA50 and the Hill coefficient set to published values for UGT1A1 ontogeny rather than estimated from this small cohort. Residual covariate effects of PNA, weight, sex, and feeding pattern will then be tested empirically. To probe the robustness of the maturation assumption, we will conduct a pre-specified sensitivity analysis re-fitting the model with at least one alternative published UGT1A1 ontogeny parameter set (1) and report the resulting impact on individual exposure estimates. Relative infant dose (RID) will be reported overall and by infant-age stratum (<9 months and 9–<12 months). Comparative growth and developmental analyses will use WHO z-scores and age-adjusted CREDI scores; longitudinal mixed-effects models will include infant age at measurement as a continuous covariate. Because exposure groups are self-selected, all comparative analyses are observational and exploratory. Primary safety results will be descriptive: counts, proportions with exact 95% confidence intervals, incidence rates, and Kaplan–Meier curves, without group-comparison p-values. Longitudinal growth and CREDI outcomes will be analysed with mixed-effects models adjusting for a minimal pre-specified set of covariates: infant age at measurement, infant sex, and site. Formal between-group inference for safety is deferred to other larger PK studies. Where feasible, we will perform sensitivity analyses to reduce imbalance, recognising limitations due to our sample size.

**Table 2. T2:** Planned data analyses aligned with study objectives in the CABMILK study.

Objective	Data analysis	Outcome

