To profile the extent of CAB transfer in breast milk and determine its pharmacokinetics in infants whose mothers receive long-acting injectable cabotegravir for HIV preexposure prophylaxis (PrEP).	We will use non-linear mixed effects models to determine the compartmental pharmacokinetics of CAB from maternal plasma to breast milk to infant plasma. We will first calculate the milk: plasma ratio to determine the average milk CAB concentration compared with the average maternal plasma concentration. Second, we will utilise individual predicted infant CAB concentrations to calculate infant overall exposure (AUC0-∞) and estimate CAB infant half-life as well as elimination rate constant. Third, we will estimate the CAB dose ingested by each infant, through breast milk, relative to the maternal dose; the relative infant dose (RID). ^ 25 ^ This RID will allow us to determine the extent of CAB breast milk exposure that would result in attained concentrations in the infant’s blood that are above or below the protein-adjusted IC90 of 0.166 μg/mL. ^ 26 ^	CAB transfer to the infant through breast milk, and profile the attained infant concentrations.
To determine the association of breast milk CAB exposure and infant safety outcomes (growth pattern, neuro-cognitive development, and incidence of adverse events).	Firstly, mean anthropometric indices (weight-for-height, height-for-age, head circumference-for-age) will be compared across three groups using independent t-tests. Secondly, adverse events (overall morbidity) by the end of follow-up will be compared across the three groups using Chi-squared tests. Age-standardised CREDI summary scores (z-scores) analysed as continuous outcomes, reported as adjusted mean differences with 95% confidence intervalsUsing linear regression, we will assess whether breast milk CAB concentrations predict growth patterns and morbidity, adjusting for infant age, sex socio-economic status, birth weight and gestation age at birth. Random effects models will account for intra- and interindividual variability in repeated measurements. Exploring this analysis may inform algorithms for monitoring CAB safety signals in infants. These algorithms could be validated in larger studies and incorporated into routine practice for early detection of CAB-related risks in infants.	Impact of CAB breast milk exposure on infant growth and neurocognitive development in comparison to the standard daily oral PrEP.

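### The between-group adverse event comparisons that the protocol names take no account of infant age, although entry spans almost five months of age and a general promise of confounder adjustment is made elsewhere

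*Protocol article*

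**What the plan says.** The Step 2 section of the protocol article states the hypothesis as "no difference in the incidence of adverse events or illnesses, growth, and development between infants exposed to breast milk CAB" and infants exposed through milk to oral PrEP. The same section describes the comparators differently. The unexposed group is "50 mother-infant pairs naïve of PrEP, matched to those in the CAB PrEP group", while the oral PrEP group is "25 other mother-infant pairs from the oral PrEP group of the PathToScale and LINK studies", with no mention of matching.

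On age, the eligibility section allows entry "from the first week of birth to less than 5 months", and Step 2 says that pairs "will be followed up for eight months from the time of maternal PrEP initiation in the PrEP groups", or from a similar time in the PrEP-naïve group.

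For the between-group comparison of adverse events, two methods are named:

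- Data analysis text: "Primary safety results will be descriptive: counts, proportions with exact 95% confidence intervals, incidence rates", together with survival curves and no p-values.
- Table 2, second objective: "adverse events (overall morbidity) by the end of follow-up will be compared across the three groups using Chi-squared tests".

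Four other statements bear on adjustment:

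- The sample size section says, without excepting adverse events, that the non-randomised analyses will be adjusted for prespecified maternal and infant confounders.
- The Data analysis text gives a covariate set of infant age, sex and site, but for growth and CREDI only. It also offers sensitivity analyses for imbalance where feasible, with no method named.
- Table 2 adjusts the regression of growth and morbidity on milk CAB concentration for infant age and other factors.
- The section on factors affecting milk exposure enters feeding pattern into the safety analyses.

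**The concern.** An infant entered in the first week is observed from about 0 to 8 months of age; one entered just before 5 months is observed from about 5 to 13 months. If background illness changes over that span, the expected number of adverse events in eight months depends on age at entry. A crude comparison of two self-selected groups then mixes any effect of exposure with any difference in age mix. It can show a difference where exposure does nothing, or mask one where it does something.

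The contrast that carries the Step 2 hypothesis, CAB versus oral PrEP, has neither stated matching nor a stated adjusted adverse event analysis. Leaving out p-values does not cure this, because the bias lies in the estimate. The objectives promise effect sizes with confidence intervals, and the dissemination plan intends the results for policy briefs and infant safety-monitoring algorithms. Age is recorded to the day at every safety assessment, so this particular source of confounding can be avoided.

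**Working it through.** **Stated inputs.** 25 CAB and 25 oral PrEP pairs; entry age from the first week to under 5 months; eight months of follow-up. Step 2 gives no adverse event rate, effect size or power, so there is no figure of the plan to reproduce.

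**Assumptions, not in the documents.** Exposure has no effect. The adverse event rate is b per month before 6 months of age and R × b afterwards. Main case b = 0.05, with R from 1.5 to 3.

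**Formulas.** An infant entered at age a months spends 6 − a months of follow-up below 6 months of age and 2 + a months above it. Then

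- cumulative hazard H(a) = b × [(6 − a) + R × (2 + a)];
- risk of at least one event p(a) = 1 − exp(−H(a));
- half-width of the 95% interval for the risk difference = 1.96 × √[p1(1 − p1)/25 + p2(1 − p2)/25].

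Example, entry at 2 versus 3 months, R = 2: H = 0.05 × (4 + 2 × 4) = 0.60 and 0.05 × (3 + 2 × 5) = 0.65. Risks are 45.1% and 47.8%, a spurious difference of 2.7 points. The rate ratio is 0.65/0.60 = 1.08.

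**Results for b = 0.05** (differences taken before rounding):

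| Entry ages (months) | R | H | Risks | Spurious difference | Half-width |
|---|---|---|---|---|---|
| 2 v 3 | 1.5 | 0.500 v 0.525 | 39.3% v 40.8% | 1.5 points | 27.2 |
| 2 v 3 | 2 | 0.600 v 0.650 | 45.1% v 47.8% | 2.7 points | 27.6 |
| 2 v 3 | 3 | 0.800 v 0.900 | 55.1% v 59.3% | 4.3 points | 27.4 |
| 1 v 4 | 1.5 | 0.475 v 0.550 | 37.8% v 42.3% | 4.5 points | 27.1 |
| 1 v 4 | 2 | 0.550 v 0.700 | 42.3% v 50.3% | 8.0 points | 27.6 |
| 1 v 4 | 3 | 0.700 v 1.000 | 50.3% v 63.2% | 12.9 points | 27.2 |

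With R = 1 the bias is zero at any age gap, and the half-width is 26.1 points.

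**Other base rates, R from 1.5 to 3.** At b = 0.02 the bias is 0.8 to 2.8 points for the 1-month gap and 2.4 to 8.5 for the 3-month gap. At b = 0.10 it is 1.8 to 3.7 and 5.4 to 11.1.

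**Does stratifying by age remove it?** In 20,000 simulated studies per scenario with no exposure effect and b = 0.05, the crude rate ratio was 1.08 (mean entry ages 2.1 v 3.0 months, R = 2), 1.17 (1.6 v 3.5 months, R = 2) and 1.25 (1.6 v 3.5 months, R = 3). The Mantel–Haenszel rate ratio stratified by attained age was 1.000, 1.003 and 1.001. The age bands here coincide with the assumed change in rate; bands that fit less well would leave some bias.

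**The case against.** The strongest reply is that the protocol neither ignores confounding nor claims inference. The sample size section promises adjustment in general, feeding pattern enters the safety analyses, sensitivity analyses for imbalance are foreseen, Step 2 is repeatedly called descriptive, and the Limitations section admits residual confounding. Both PrEP groups come from the same parent studies through the same age window, so their mean ages may be close. A 1-month gap then gives a bias far smaller than sampling error.

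Most of that stands and limits the size of the point. It does not remove it: the general promise is not carried into either adverse event method actually named, feeding pattern is not infant age, and the sensitivity analyses are conditional and undefined.

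Several stronger readings are tempting but unsupported:

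- *The PrEP-naïve comparison is protected against age imbalance and the oral PrEP comparison is not.* No matching factor is named in the article, so age matching is not shown for either group. An article may leave such factors to the full protocol or analysis plan.
- *The CAB and oral PrEP infants will differ in age.* Nothing in the document shows this.
- *The study will have an inflated false-positive rate for adverse events.* The Data analysis text says that no group-comparison p-values will be given. Table 2's chi-squared test conflicts with that, but it is a matter of reconciling the text and no basis for an error rate.
- *Failing to use the matching undermines the CAB versus PrEP-naïve result.* Ignoring matched sets in a cohort does not bias the group difference. At most it costs some precision, by an amount that cannot be judged without the factors.

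**Conclusion.** The point holds for adverse events. Every between-group method named is unadjusted, the hypothesised contrast has no stated matching, and the general promise of adjustment is inconsistent with those methods. The plan already treats age as relevant to morbidity when it relates morbidity to milk concentration, but not when it compares groups on adverse events.

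The size is unknown and may be nil. Bias needs both a difference in age mix and an adverse event rate that changes with age. Under the main assumptions it is about 1.5 to 4 points for a 1-month gap in mean entry age and about 4.5 to 13 points for a 3-month gap, against a half-width of about 26 to 28 points. A small gap would therefore be lost in sampling error, while a large one could account for much of an apparent signal.

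A reader might extend the point to growth and development. The document does not support that: growth uses WHO z-scores, CREDI scores are age-standardised, and both have models that include infant age.

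**What to change.** In the Data analysis text and Table 2, report the CAB versus oral PrEP adverse event rate ratio or risk difference with a 95% confidence interval, either stratified by attained-age band or adjusted for infant age and site. Place it beside the crude counts, and do the same for CAB versus PrEP-naïve. Keep the presentation descriptive. Then align the sample size section, the Data analysis text and Table 2, so that the promise of adjustment, the named adverse event methods and the position on p-values agree.

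The cost is a change of wording and one extra table or small model, using ages already recorded to the day; recruitment is unaffected. The price is slightly less stable estimates with 25 infants per group, so the age bands should be few and the covariate set small.

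### The PrEP-naïve pairs are said to be matched to the CAB-LA pairs, but Table 2's t-tests and chi-squared tests ignore the matching, and the mixed models use it only if the matching factors lie within infant age, sex and site

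*Protocol article*

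**What the plan says.** The Step 2 section of the protocol article describes the unexposed comparison group in these terms: "50 mother-infant pairs naïve of PrEP, matched to those in the CAB PrEP group, will be followed up for eight months". This is the only mention of matching. Study design and population, and Sample size determination and power calculation, give the same group sizes (25 CAB-LA, 25 oral PrEP, 50 PrEP-naïve) without it.

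The analyses are named in the Data analysis section and its Table 2:

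- **Growth, Table 2 (second objective):** mean anthropometric indices "will be compared across three groups using independent t-tests".
- **Adverse events, Table 2:** these "will be compared across the three groups using Chi-squared tests".
- **Longitudinal growth and CREDI, Data analysis text:** "mixed-effects models adjusting for a minimal pre-specified set of covariates: infant age at measurement, infant sex, and site".
- **Random effects, Table 2:** "Random effects models will account for intra- and interindividual variability in repeated measurements". They serve repeated measures, not matched sets.
- **Primary safety results, Data analysis text:** counts, proportions with exact intervals, incidence rates and Kaplan–Meier curves, with no p-values between groups.

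The specific aims promise effect sizes with 95% confidence intervals and no formal testing between groups. The sample size section adds that comparisons will be adjusted for prespecified maternal and infant confounders, without listing them there.

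**The concern.** Matching makes the compared infants alike on the matching factors. If those factors predict the outcome, the CAB-LA and PrEP-naïve group means are positively correlated and their difference varies less than it would for independent samples. An independent-samples analysis ignores this, so its standard error for the difference is too large and its 95% interval covers more than 95% of the time.

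This does not depend on whether p-values are reported. It also applies to the intervals that the specific aims make the main comparative result. With only 25 exposed infants, an interval that is wider than the design requires makes a growth or morbidity difference harder to see, which is an unhelpful direction of error in a safety description.

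The text shown states a matched design and then names tests for unmatched samples. That mismatch is the point. The absence of a list of matching factors is not, because the statistical analysis plan may give one.

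**Working it through.** **1. Does any named analysis use the matching?**

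| Analysis | Uses the matching? |
|---|---|
| Independent t-tests (Table 2) | No |
| Chi-squared tests (Table 2) | No |
| Mixed models with age, sex, site (Data analysis) | Yes, if the matching factors are among these three; otherwise not fully |
| Random effects (Table 2) | No; they are for repeated measures |
| Exact intervals for each group's proportion | Not relevant; no contrast is involved |

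Other sections name further variables: gestational age under the exclusion criteria, feeding pattern under the pharmacokinetic procedures, and socio-economic status, birth weight and gestation in Table 2's regression on milk concentration. A matching factor of that kind would lie outside the three covariates listed for the mixed models.

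**2. How much wider is the independent interval?**

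The plan states no precision or power for this contrast, so there is no figure to reproduce.

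Inputs from the document: 25 CAB-LA and 50 PrEP-naïve infants, 95% confidence.

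Assumed: individual 1:2 matching, common SD of 1, exchangeable within-set correlation ρ.

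Variance of the mean difference:

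- Independent: 1/25 + 1/50 = 0.06, so SE = 0.2449.
- Matched: (1/25)[1 + (1+ρ)/2 − 2ρ] = 0.06(1−ρ), so SE = 0.2449·√(1−ρ).

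The half-width is the SE times the 97.5% t quantile, with 73 degrees of freedom (independent) or 24 (25 set-level differences).

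| ρ | Independent half-width (SD) | Set-level half-width (SD) | Ratio |
|---|---|---|---|
| 0 | 0.488 | 0.506 | 0.97 |
| 0.05 | 0.488 | 0.493 | 0.99 |
| 0.1 | 0.488 | 0.480 | 1.02 |
| 0.2 | 0.488 | 0.452 | 1.08 |
| 0.3 | 0.488 | 0.423 | 1.15 |
| 0.5 | 0.488 | 0.357 | 1.37 |

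The two are equal at ρ = 1 − (t₇₃/t₂₄)² ≈ 0.07. Below that the set-level interval is the wider one. The standard-error ratio 1/√(1−ρ) gives 1.12, 1.20 and 1.41 at ρ = 0.2, 0.3 and 0.5, but it overstates the effect on the interval because it leaves out the lost degrees of freedom.

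**3. Does covariate adjustment recover the precision?**

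A simulation with 10,000 runs per ρ used one matching factor, shared within sets, that explains a fraction ρ of the outcome variance. Entries are coverage and mean half-width in SD.

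| ρ | Independent t | Adjusted for the factor | Set-level |
|---|---|---|---|
| 0.1 | 0.958; 0.486 | 0.947; 0.461 | 0.946; 0.473 |
| 0.2 | 0.970; 0.486 | 0.950; 0.435 | 0.949; 0.448 |
| 0.3 | 0.978; 0.485 | 0.950; 0.407 | 0.948; 0.419 |
| 0.5 | 0.993; 0.485 | 0.948; 0.344 | 0.949; 0.354 |

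Adjusting for the matching factor restores nominal coverage and gives intervals slightly narrower than the set-level analysis. It needs no sets, so it also works under frequency matching.

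**The case against.** **The matching is barely described.** The document does not say whether it is individual or by frequency, at what ratio, or on which factors. The sample size section gives a different reason for having 50 unexposed pairs: steadier estimation of background patterns. A reader might infer 1:2 matched sets from 50 and 25, but the text does not say so. Under frequency matching there are no sets, and a set identifier or set-level analysis has nothing to act on. This stands, and it is why covariate adjustment is the main remedy.

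**The mixed models may already deal with it.** A reader might infer that every named analysis ignores the matching. That is too strong: if the factors are any subset of age, sex and site, the growth and CREDI models use them. This stands for those models. It does not help the t-tests or chi-squared tests.

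**The correlation may be small.** Growth and CREDI outcomes are age-standardised, so matching on age would leave little correlation. This also stands. Nothing in the documents supports a value as high as 0.5; it is only the top of the range shown.

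**Step 2 is descriptive.** The aims and the Data analysis text rule out formal testing, so false-positive rates or power for the Table 2 tests would describe analyses that those sections say will not be done. If Table 2 is reconciled with that text by dropping the tests, the clearest cases disappear. What remains is that the aims still promise effect sizes with intervals, and an interval for a contrast has to reflect the design.

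**Conclusion.** The concern holds in a limited form. The document states matching, Table 2's unadjusted comparisons ignore it under either individual or frequency matching, and the mixed models use it only if the factors fall within age, sex and site.

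The effect is conservative intervals for the CAB-LA versus PrEP-naïve contrast: about 8% to 15% too wide at correlations of 0.2 to 0.3, 37% at 0.5, and no gain from a set-level interval below about 0.07. These figures rest on assumed 1:2 individual matching and an assumed correlation.

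A reader might go further and conclude that the planned safety intervals are wrong throughout, or that the estimates are biased. The documents do not support either. Ignoring the matching does not by itself bias the mean difference, and the exact intervals for single-group proportions are unaffected. In an exploratory step the consequence is modest, but it is nearly free to correct.

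**What to change.** In the Data analysis section and Table 2:

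1. Include every matching factor as a covariate in the growth and CREDI mixed models for CAB-LA versus PrEP-naïve, and the same factors for CAB-LA versus oral PrEP, so that both contrasts adjust alike.
2. Replace the independent t-tests and chi-squared tests with estimates and 95% intervals adjusted for or stratified by those factors, for example a Mantel-Haenszel or regression risk difference for adverse events.
3. If matching is individual, record the set identifier at enrolment and consider a matched-set random intercept. Study status reports that recruitment has been under way since September 2025, and sets may be hard to rebuild later. Avoid a purely conditional set-level analysis: it drops controls whose CAB-LA member is lost, and the Missed visits section expects missed visits.
4. If no matching is done, delete the word from the Step 2 section.

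The cost is wording and, for individual matching, one extra variable. No participants or procedures are added. The downside is a few degrees of freedom, and slightly wider intervals if the matching factors turn out to be unrelated to outcome.
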